#### Inclusion criteria

2.2.2

Patients who (1) are aged ≥18 years; (2) are diagnosed with AMI (I21of ICD-10 standard); (3) have received PCI; (4) participate in the home-based phase 2 CR; (5) can speak, read, and understand Mandarin; and (6) are willing to participate in this survey.

#### Exclusion criteria

2.2.3

Patients who (1) have complications from PCI and (2) participate in the phase 2 CR program in the hospital as outpatients will be excluded.

#### Research instrument

2.2.4

##### The demographic data sheet (DDS)

2.2.4.1

The researcher will develop a DDS, which will include two parts: demographic data, such as age, sex, marital status, educational level, employment status, and smoking status, and history of illness, such as diabetes, dyslipidemia, length of stay, D2B time, and arrhythmia during PCI. The DDS will be a form of open-ended and closed-ended questions.

##### The center for epidemiological studies depression scale (CES-D-S)

2.2.4.2

Feng et al. (47) developed a Chinese version of the CES-D-S to measure depression. This scale contains four dimensions with 10 items: physical factors, interpersonal relationships, negative emotions, and positive emotions. The I-CVIs ranged from 0.830–1.000, while the S-CVI was 0.86. CFA showed that the structural validity model achieved adaption (RMSEA <0.08, GFI and CFI >0.90, and CMIN/df <3) (47). Each item is rated on a 4 Likert scale from 0 to 3, with a total score range of 0–30 points. The higher the score, the more severe the depression.

##### The multidimensional scale of perceived social support (MSPSS)

2.2.4.3

The MSPSS evaluates perceived social support and was translated into Chinese by Chen et al. (48). The Chinese Version of the MSPSS has 12 items with three dimensions: family support, friend support, and other important support. The CFA of this scale supported a three-factor first-order model that fit well (RMSEA = 0.070, CFI = 0.941, and *χ*^2^/*df* = 2.753) (48). Each item is rated on a 7 Likert-type scale, where 1 means “strongly disagree,” and 7 means “strongly agree.” The total score ranges from 12 to 84 points. Higher scores represent higher perceived social support.

##### The coronary artery disease health belief scale (HBMS)

2.2.4.4

The HBMS was developed by Zhang et al. (49) in Chinese based on the HBM to assess patients' health beliefs related to behavior change. It contains five dimensions: perceived susceptibility, perceived seriousness, perceived benefit, perceived barriers, and cues to action. with 27 items. Eight common factors were extracted from the EFA of this scale, and the cumulative variance contribution rate was 60.698%. The correlation between the subscales and the total scale ranged from 0.811 to 0.876 (49). Each item was rated on a 5 Likert–type scale ranging from 1 (strongly disagree) to 5 (strongly agree). The total score ranged from 27 to 135. Higher scores indicate higher health beliefs.

##### The Chinese version of the cardiac self-efficacy scale (C-CSES)

2.2.4.5

The C-CSES was developed by Zhang et al. (50) and was translated from the CSEQ developed by Sullivan et al. (51) includes 13 items with three dimensions: control illness, control symptoms, and maintain function. The I-CVIs of this scale ranged from 0.81–0.96, while the S-CVI was 0.87. Confirmatory factor analysis (CFA) supported a three-factor high-order structure of the C-CSES with model fit indices: RMSEA = 0.084, CFI = 0.954, NNFI = 0.927, IFI = 0.954 and *χ*^2^/*df* = 2.572 (50). Each item was rated on a 5 Likert–type scale ranging from 0 (not at all) to 4 (completely confident). The total score ranged from 0 to 52 points. Higher scores indicate higher self-efficacy.

##### The scale of adherence to cardiac rehabilitation (ACRS)

2.2.4.6

The ACRS was developed by Wen, X.H. (52) based on quality interviews and literature reviews to assess adherence to CR in CHD patients. The ACRS contains 33 items with five subscales: exercise, medication, risk factors, nutritional, and psychological management. The I-CVIs of the scale ranged from 0.80–1.00, while the S-CVI was 0.96. The cumulative variance contribution rate was 60.698%, and the CFA showed good structural validity: *X*^2^ < 0.001, RMSEA = 0.055, CFI = 0.851 (52). The scale responds “yes” or “no” for each item (yes = 1 point, no = 0 points). The total score range of the scale is 0–33 points. The total score is classified into high and low: 33–25 points indicates high adherence to cardiac rehabilitation and 24–0 indicates low adherence to cardiac rehabilitation (45).

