#### Sample size and sampling method

2.2.1

According to the suggestion of Nunnally and Bernstien, selecting 5–10 participants per item is appropriate for multivariate analysis (46) 165 participants will be recruited to unitize the factor analysis for the 33 items of the Scale of Adherence to Cardiac Rehabilitation scale (ACRS). Considering a follow-up attrition rate of 20%, this number will increase to 198.

Following the approval of the research project by the Ethics Committee of the two hospitals, the study will be conducted on 198 participants with AMI after PCI one month after discharge who receive home-based OCR. The researchers will visit two hospitals, identify eligible patients using the hospital information system (HIS) following the proportion (70% and 30%) of the target population in two hospitals, explain the study objectives and brief process to them, and obtain informed consent to participate. Patients will complete the Demographic Data Sheet (DDS).

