#### Data analysis

2.2.6

IBM SPSS 22.0 software will be used for data analysis. Statistical significance will be set at *p* < 0.05. The data analysis process was as follows:

The independent variables, including demographic variables, psychological characteristics, and the six constructs of the HBM, are described using frequency, percentage, mean, and standard deviation.

Dummy coding will be performed for categorical data. The assumption of logistic regression, including linearity, homoscedasticity, and residual normality, will be checked before entering the data into SPSS. Linearity: The partial regression plot between dependent and independent variables should be random. Homoscedasticity: Check the residual plot of the dependent variable; the scatter plot should be random without a curve pattern. Normality of residuals: Check the histogram of the dependent variable and a standard probability plot. Univariate analysis and binary logistic multivariate statistical analysis will be used to calculate the regression coefficient, odds ratio (OR), and 95% confidence interval of each variable using the stepwise entry method, and the independent risk factors related to adherence to home-based phase 2 CR will be analyzed.

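### The only multivariable model uses the 0–33 adherence score cut at 25, which gives up about 36–72% of the outcome information depending on the split; modelling the full score would be a cheap improvement

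*Protocol article*

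**What the plan says.** Section 2.2.4.6 of the protocol article describes 33 yes/no items, one point for each yes: "The total score range of the scale is 0–33 points". It then divides the total in two: "The total score is classified into high and low". The threshold, for which a source is cited, is that "33–25 points indicates high adherence to cardiac rehabilitation and 24–0 indicates low adherence to cardiac rehabilitation".

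Section 2.2.6 sets out the search for influencing factors: "Univariate analysis and binary logistic multivariate statistical analysis will be used to calculate the regression coefficient". Odds ratios with 95% confidence intervals follow, and variables enter stepwise. The section does not name the dependent variable. The high/low class is the only binary form of adherence that the article defines, so it must be the outcome. No regression on the total is mentioned.

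Phase two uses both forms. Section 2.3.1 picks interviewees from the top and bottom 10% of ACRS scores, and section 2.3.2 recruits from the high- and low-adherence groups.

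**The concern.** Finding the factors that influence adherence is part of objective 1. The instrument gives 34 possible values per patient, but the model sees only two. A patient scoring 24 is treated like one scoring 0 and unlike one scoring 25. A factor that moves patients several points within the low band, or within the high band, contributes nothing.

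The full score is collected anyway and is used to choose interviewees, so dropping it from the model saves no effort. The loss falls on power. The interview guide is to be built on the phase-one findings (section 2.3.2), so factors missed in phase one are less likely to be explored in phase two.

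**Working it through.** **The plan's own figure.** Section 2.2.1 takes 5 participants for each of 33 items: 5 × 33 = 165, raised by 20% for attrition, 165 × 1.20 = 198. Both reproduce. The rule is one of participants per item ("selecting 5–10 participants per item is appropriate for multivariate analysis"), so no target effect or power is stated against which to set a loss. I use the base figure of 165; the percentage loss does not depend on it.

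**Inputs from the article**
- Score range 0–33 and cut at 25: section 2.2.4.6.
- Significance level 0.05: section 2.2.6. Two-sided testing is my assumption.
- Adherence rates of 7.05–29.9% in China, and 22–80% in the sentence on home-based rehabilitation abroad: section 1, Background.

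**Assumptions, not in the article**
- The share *p* scoring 25 or more. The Background rates serve only as a proxy, so an even split is shown as well.
- A roughly normal score, linearly related to the predictor.
- A single predictor with correlation *r* = 0.20, for the power figures.

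**Information kept after the cut.** For a normal score cut so that a share *p* is high, the asymptotic relative efficiency is φ(z)² / [p(1 − p)], where φ is the standard normal density and z the *p* quantile.

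| Share high | φ(z)² | p(1 − p) | Efficiency | Loss | 165 patients act like |
|---|---|---|---|---|---|
| 50% | 0.1592 | 0.2500 | 0.637 | 36% | 105 |
| 29.9% | 0.1205 | 0.2096 | 0.575 | 42% | 95 |
| 7.05% | 0.0182 | 0.0655 | 0.278 | 72% | 46 |

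For the foreign range, the efficiency is 0.511 at 22% (loss 49%) and 0.490 at 80% (loss 51%). The loss is smallest at 50%, so that range spans about 36–51%.

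**Check on a discrete score.** A 0–33 beta-binomial score with an assumed intra-item correlation of 0.1, cut at 25, lost about 35–57% for shares from 15% to 70%. The result does not depend on treating the score as continuous, although a score piled up at one end would change it.

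**Power.** Simulation with n = 165, one predictor, *r* = 0.20 and two-sided 5%, comparing a correlation test on the full score with a logistic score test on the cut score:
- full score: about 73%;
- cut, 50% high: about 53%;
- cut, 29.9% high: about 50%;
- cut, 7.05% high: about 25%.

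A rerun with 40,000 replicates gave 74%, 54%, 50% and 27%, so these figures are good to a point or two.

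**The case against.** The strongest reply is that the threshold is neither arbitrary nor data-driven. It is pre-specified and cited, it answers the question about the level of adherence, and it matches the groups from which interviewees are recruited. Modelling the same class that the qualitative phase uses is defensible in an explanatory sequential design. This stands, and it is why the cut should be kept for those purposes. It does not explain why the cut should be the only outcome form when looking for influencing factors.

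The size of the loss is also uncertain. The Background rates are not tied to the 25-point cut, and section 2.2.2 admits only patients already taking part in home-based rehabilitation, so the share scoring high could be well above the Chinese rates. A reader might infer that this study will lose 70% of its information; that rests on the single 7.05% figure, and the article does not support it as a forecast. The correlation of 0.20 and the single predictor are illustrative too, since the plan is for a multivariable model.

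A reader might also take the checks in section 2.2.6 (homoscedasticity, residual normality) as proof that a model of the full score was intended. The article labels them as logistic assumptions. They are a separate drafting matter and do not show that cutting the score is wrong.

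**Conclusion.** The concern holds as one of efficiency. The full score is left out of the only multivariable model, and under approximate normality the cut costs about 36–72% of the outcome information depending on the split, with 36% as the best case. In the illustrative setting, power drops by about 20 points (73% to 53%) at an even split and by more at an uneven one. These sizes rest on an unstated share scoring high, on normality and on an assumed correlation.

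It would go too far to call the planned analysis invalid. A logistic model on a pre-specified, cited threshold answers a legitimate question. The dependent variable is inferred and not stated, but the article offers no other binary outcome. This is a cheap improvement.

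**What to change.** In section 2.2.6, name the ACRS total as the outcome of the main influencing-factors model. Use linear regression with robust standard errors, or overdispersed binomial regression on the number of items out of 33 if the score is skewed or sits at its ceiling. Keep the logistic model for 25 or more as a named secondary analysis. Keep the cut in section 2.2.4.6 for describing the level of adherence, and in phase two for forming the interview groups.

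The cost is analysis wording only: no new data, patients or visits. The downside is that the main effects are then in score points, and the odds ratio for high adherence becomes a secondary result.

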#### Data collection

2.2.5

This study will collect quantitative data using questionnaires. The following stages will be implemented to complete the data collection process.
(1)After obtaining permission from the directors of each hospital, the researcher will ask one research coordinator from the cardiac clinic of each hospital and a quiet, private room at the cardiac clinic to collect the form and questionnaires.(2)The researcher will prepare 200 packages, each containing a form and five questionnaires, and explain the data collection process to the research coordinators.(3)The researcher will obtain a list of STEMI PCI patients for follow-up at the outpatient department. The researcher will screen eligible patients and assign numerical codes to replace the patients' names. Subsequently, the researcher will provide a coded list to the research coordinators for subject selection.(4)The research coordinator will schedule an appointment in advance for potential patients at the cardiac clinic after they meet the doctor and explain the study's purposes, procedures, duration, and benefits. If the subjects agree to participate, they will be requested to sign a consent form.(5)The research coordinator distributes the research package to all participants. Each participant will spend 45–60 min completing the questionnaires and will then return the questionnaires and consent form separately in two designated boxes within the room. The research coordinator then checks for the completeness of all documents collected from the boxes and returns them to the researcher every week.

#### Data analysis

2.2.6

IBM SPSS 22.0 software will be used for data analysis. Statistical significance will be set at *p* < 0.05. The data analysis process was as follows:

The independent variables, including demographic variables, psychological characteristics, and the six constructs of the HBM, are described using frequency, percentage, mean, and standard deviation.

Dummy coding will be performed for categorical data. The assumption of logistic regression, including linearity, homoscedasticity, and residual normality, will be checked before entering the data into SPSS. Linearity: The partial regression plot between dependent and independent variables should be random. Homoscedasticity: Check the residual plot of the dependent variable; the scatter plot should be random without a curve pattern. Normality of residuals: Check the histogram of the dependent variable and a standard probability plot. Univariate analysis and binary logistic multivariate statistical analysis will be used to calculate the regression coefficient, odds ratio (OR), and 95% confidence interval of each variable using the stepwise entry method, and the independent risk factors related to adherence to home-based phase 2 CR will be analyzed.

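### Hospital is not named or forced into the stepwise logistic model, so any hospital effect on adherence could be reported as an independent patient-level factor

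*Protocol article*

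**What the plan says.** All references are to the protocol article.

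- **Recruitment (2.2.1).** Eligible patients are identified "following the proportion (70% and 30%) of the target population in two hospitals".
- **Data collection (2.2.5).** Each site has its own contact: "the researcher will ask one research coordinator from the cardiac clinic of each hospital". That coordinator makes the appointments, explains the study, obtains consent, hands out the questionnaire packages and checks them for completeness.
- **Predictors (2.2.6 and 2.2.4.1).** The analysis section refers to "The independent variables, including demographic variables, psychological characteristics, and the six constructs of the HBM". The demographic data sheet collects "demographic data, such as age, sex, marital status, educational level, employment status, and smoking status", and under illness history it adds diabetes, dyslipidaemia, length of stay, D2B time and arrhythmia during PCI. Neither list names hospital.
- **Model (2.2.6).** Univariate analysis is followed by binary logistic regression with stepwise entry, at p<0.05. The stated purpose is to identify independent risk factors. No variable is said to be kept in the model regardless of the selection.
- **Outcome (2.2.4.6).** The adherence score is split into high (25-33) and low (0-24).

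**The concern.** Hospital is a design variable. It determines where a patient was treated, who recruited them and who administered the questionnaires. It can also be related to candidate factors: length of stay and D2B time depend partly on the hospital's own practice, and the background section cites both as influences on adherence in earlier studies.

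If adherence also differs between the hospitals, a pooled model without a hospital term can credit that difference to a patient-level factor. Stepwise selection adds to the problem. Even if hospital were among the candidates, it could be dropped while a factor that stands in for it is kept.

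The result matters beyond the regression table. Phase-one findings shape the interview guide (2.3.2) and feed the strategies in phase three (2.4). A service difference read as a patient trait would direct the strategy at the wrong target.

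**Working it through.** **1. The plan's own figures.** The sample size follows an items rule: "selecting 5–10 participants per item is appropriate for multivariate analysis". At 5 per item, 33 × 5 = 165, and 165 × 1.2 = 198, which is the stated total. The expected split is 198 × 0.70 = 138.6 and 198 × 0.30 = 59.4, or about 139 and 59 patients; for 165 it is 115.5 and 49.5. The sample size does not depend on the model, so adding a hospital term leaves it unchanged.

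**2. The mechanism, by hand.** Take a binary factor X with no effect within either hospital. The hospital differences below are assumptions; the documents give none. Hospital A supplies 70% of patients and hospital B 30%.

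P(high | X=1) = [0.7·P(X=1|A)·P(high|A) + 0.3·P(X=1|B)·P(high|B)] / P(X=1), and likewise for X=0.

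- *Case 1:* X in 60% v 40%, high adherence in 35% v 20%.
  - X=1: (0.7×0.6×0.35 + 0.3×0.4×0.20)/0.54 = 0.171/0.54 = 0.317.
  - X=0: (0.7×0.4×0.35 + 0.3×0.6×0.20)/0.46 = 0.134/0.46 = 0.291.
  - Pooled OR = (0.317/0.683)/(0.291/0.709) = 1.13.
- *Case 2:* X in 70% v 30%, high adherence in 40% v 15%.
  - X=1: (0.196 + 0.0135)/0.58 = 0.361.
  - X=0: (0.084 + 0.0315)/0.42 = 0.275.
  - Pooled OR = 1.49.

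The true OR is 1 in both cases. Case 1 implies a hospital OR for adherence of (0.35/0.65)/(0.20/0.80) = 2.15. Case 2 implies (0.40/0.60)/(0.15/0.85) = 3.78, which is a large difference.

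**3. False-positive rate, by simulation.** There were 2,000 runs per scenario, with n = 165 and 198 split 70/30 and one continuous covariate with no true effect, tested two-sided at 0.05. Assumptions: 30% high adherence in the larger hospital (close to the top of the 7.05%-29.9% range the article cites for China), a hospital OR of 1 to 3, and a covariate difference between hospitals of 0 to 0.8 SD. With 30% in the larger hospital, ORs of 1.5, 2 and 3 imply 39%, 46% and 56% in the smaller one (for OR 2: odds 0.429 × 2 = 0.857, and 0.857/1.857 = 0.46).

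| Hospital OR | Covariate difference | p<0.05, hospital omitted |
|---|---|---|
| 1, or any OR with no covariate difference | 0-0.8 SD | 4.2%-5.5% |
| 1.5 | 0.3-0.8 SD | 5.1%-7.3% |
| 2 | 0.3-0.5 SD | 5.9%-7.6% |
| 3 | 0.3 SD | 7.7% |
| 2 | 0.8 SD | 10.1%-11.9% |
| 3 | 0.5 SD | 11.3%-12.0% |
| 3 | 0.8 SD | 19.4%-22.6% |

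Where both differences are present, the mean spurious OR per SD runs from 1.03 to 1.19. With hospital included, the rate is 4.1%-6.1% in all 32 scenarios and the mean OR is 0.99-1.01. Simulation error near 5% is about ±1 percentage point (2 × √(0.05 × 0.95/2000) = 0.0097), so the lowest rows can hardly be told apart from nominal.

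The simulation fits one covariate at a time. It does not reproduce the stepwise procedure or a model with many covariates, so it shows the direction and rough size of the effect and does not forecast this study's error rate.

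**The case against.** The strongest reply is that the article does not say hospital is left out. The sentence listing the independent variables introduces their descriptive summary and does not specify the model. Both variable lists are open-ended, and a condensed article may leave the full covariate list to another document. That stands as far as it goes: the text does not name hospital, but it does not exclude it. What remains is the selection rule, which the article does state. Under stepwise entry a design variable has no guaranteed place, even if it is a candidate.

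A reader might infer from the 70/30 recruitment that the sampling itself biases the results. It does not. Taking patients in proportion to the target population is self-weighting, and the pooled adherence level is not distorted by it.

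A reader might also infer that the reported factors are certain to be confounded. The documents do not support that. Confounding needs a hospital difference in both adherence and the factor, and no section shows either. Some features point towards similarity: both sites are tertiary hospitals in one city, all participants follow home-based rehabilitation, and the same researcher briefs both coordinators on the same packages. In addition, where a hospital acts on adherence only through a measured factor already in the model, such as self-efficacy, that route does not confound the factor.

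Finally, the effect is small for modest differences. That is correct, and it limits the weight of the point.

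**Conclusion.** The point holds as a worthwhile, inexpensive improvement. The stated analysis does not ensure that hospital is adjusted for, so it cannot by itself support calling the selected factors independent of hospital. Length of stay and D2B time deserve most caution.

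The size depends entirely on assumed hospital differences: a false-positive rate of about 5-8% for modest ones and about 10-23% for large ones, against about 5% with hospital included. If the hospitals are alike in adherence, or alike in the factor concerned, there is no bias. The large-difference scenarios assume 46% or 56% high adherence in the smaller hospital against 30% in the larger, and nothing in the article shows a gap of that size.

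**What to change.** In section 2.2.6, state that hospital is recorded for every patient and forced into the multivariable logistic model as a fixed covariate, outside the stepwise selection. With two sites a random effect would not be useful. The univariable screen can stay as it is, or hospital-adjusted estimates can be shown beside it. Adherence by hospital may be reported descriptively next to the overall level.

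The cost is one degree of freedom and one sentence, since hospital is already known for each patient and the total of 198 is unaffected. Intervals become slightly wider for factors that differ strongly between hospitals. For a covariate differing by d SD, the standard error grows by roughly √(1 + 0.7 × 0.3 × d²): about 1% at 0.3 SD, 3% at 0.5 SD and 7% at 0.8 SD, and somewhat more if hospital itself strongly predicts adherence.

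### The assumption checks planned for the binary logistic regression belong to linear regression; linearity should be checked on the logit scale instead

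*Protocol article*

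**What the plan says.** Section 2.2.6 (Data analysis) of the protocol article sets out the assumption checks: "The assumption of logistic regression, including linearity, homoscedasticity, and residual normality, will be checked before entering the data into SPSS". It then names a tool for each.

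- To judge linearity, the analyst is given this criterion: "The partial regression plot between dependent and independent variables should be random".
- To judge whether the variance is constant, the instruction is: "Check the residual plot of the dependent variable; the scatter plot should be random without a curve pattern".
- For the distribution of the residuals, the tool is a histogram of the outcome itself, together with a probability plot.

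The model follows in the same paragraph: "Univariate analysis and binary logistic multivariate statistical analysis will be used to calculate the regression coefficient, odds ratio (OR), and 95% confidence interval". Section 2.2.4.6 shows where the two outcome classes come from: "The total score is classified into high and low: 33–25 points indicates high adherence to cardiac rehabilitation and 24–0 indicates low adherence". No linear model of the 0–33 total is described anywhere in the article.

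**The concern.** The three assumptions and their plots are those of ordinary linear regression with a continuous outcome. The planned model is for a two-class outcome. Two of the three assumptions do not apply to it, and the third is checked on the wrong scale.

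This regression delivers the quantitative half of the first objective (section 1.2). Its findings then feed the interview guide (section 2.3.2) and the strategies of phase three (section 2.4). An analyst who follows the text will see plots that look wrong even when the model is right, and may transform, categorise or drop sound variables in response. Meanwhile the assumption that could distort the odds ratios is not examined in a form that could reveal a problem: the shape of the relation with age, door-to-balloon (D2B) time, length of stay and the scale scores.

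**Working it through.** No figure in the plan is disputed here, so there is none to reproduce. The check takes each stated diagnostic in turn and asks what it shows when the logistic model is correct.

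**Inputs from the article.** Outcome: ACRS 25–33 versus 0–24 (2.2.4.6). Model: binary logistic (2.2.6). Sample sizes (2.2.1): 33 × 5 = 165 before the allowance for attrition, and 165 × 1.2 = 198 after it. The adherence rates cited for China in the Background, 7.05% to 29.9%, serve only as assumed proportions in the high class; 50% is a further assumption.

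**Normality.** The dependent variable takes the values 0 and 1, so its histogram has two bars whatever the data.

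**Residual plot.** For a patient with fitted probability p, the raw residual is 1 − p if the outcome is 1 and −p if it is 0. Only two values are possible at each p, so the plot is always two bands and never a random cloud.

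**Variance.** p(1−p)² + (1−p)p² = p(1−p).

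| p | p(1−p) | 0.25 divided by this |
|---|---|---|
| 0.05 | 0.0475 | 5.26 |
| 0.10 | 0.09 | 2.78 |
| 0.30 | 0.21 | 1.19 |
| 0.50 | 0.25 | 1.00 |

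The variance must change with any predictor that changes p. How much depends on the range of p: the ratio is 5.26 between 0.05 and 0.50, but only 1.19 between 0.30 and 0.50.

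**Linearity.** The model is log[p/(1−p)] = a + b₁x₁ + b₂x₂ + …, so linearity is required of the log odds. A partial regression plot works with the 0/1 outcome itself, so it is banded and sits on the probability scale. Its slope also reflects the adjusted association. A plot with no pattern would therefore mean that the predictor is unrelated to adherence, not that the relation is linear.

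**Simulation of correct models.** Settings: n = 165 and 198; prevalence 7.05%, 29.9% and 50%; three standard-normal predictors with log-odds slopes (0.5, 0.5, 0.3) or (1.0, 0.7, 0.5), all assumed; 500 runs per setting, of which 492 to 500 were usable. The share of correct models flagged at the 5% level was:

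| Check | Prevalence 7.05% and 29.9% | Prevalence 50% |
|---|---|---|
| Shapiro-Wilk on the 0/1 outcome | 100% | 100% |
| Shapiro-Wilk on raw residuals | 100% | 75.6–100% |
| Shapiro-Wilk on deviance residuals | 100% | 98.6–100% |
| Breusch-Pagan on a linear fit of the 0/1 outcome | 49.4–95.4% | 8.8–13.8% |
| Quadratic term on the logit scale | 2.4–5.4% | 4.0–5.0% |

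The average ratio of the 95th to the 5th percentile of p(1−p) ran from 1.67 to 41.45. The last row shows that a logit-scale check leaves a correct model alone at about the nominal rate. It does not measure how often that check would detect a wrong one.

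**Size of the smaller class.** At 7.05%: 165 × 0.0705 = 11.6 and 198 × 0.0705 = 14.0 patients. At 29.9%: 49.3 and 59.2.

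**The case against.** The strongest reply is that the harm is conditional. Section 2.2.6 gives no threshold and no consequence for a failed check, and it goes on to the logistic model regardless. If the plots are drawn and set aside, every coefficient, odds ratio and interval is unchanged. This stands, and it limits the severity.

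Three stronger readings are tempting, and the document does not support them.

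- A reader might infer that a correct model is certain to fail every listed check. That is strict only for the histogram of a 0/1 outcome and for the banded residual plot. Unequal variance is built in once a predictor matters, but it can be mild: near 50% prevalence a formal test flagged it in only 8.8–13.8% of runs. The article also names plots, not formal tests.
- A reader might infer that collinearity, separation, influence and calibration will not be examined. The article is condensed and its list is introduced as non-exhaustive, so these checks are unnamed, which is not the same as excluded.
- A reader might make much of residuals being inspected before data entry. Residuals exist only after a model is fitted, but SPSS is also the named analysis software, so this is most likely loose wording.

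It is also fair to say that the plan is partly right on linearity: the assumption is genuine, and only the diagnostic is wrong. None of this rescues the statement that logistic regression assumes constant variance and normal residuals.

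**Conclusion.** The point holds as an error in the text, not as missing detail: the plan attributes two false assumptions to its own model and assesses the third with a plot that cannot show it. The logical part (two-bar histogram, two-band residuals, variance p(1−p), linearity on the logit scale) needs no assumption beyond the binary outcome. The simulated percentages rest on the assumed prevalences and slopes and serve as illustration.

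A reader might infer that the reported odds ratios will be biased. Nothing in the article supports that: the checks alone change no estimate. The risk lies in acting on them and in leaving the functional form unverified. This should be fixed before analysis, but it is not a fault that invalidates the study.

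**What to change.** In section 2.2.6:

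1. Delete the homoscedasticity and residual-normality checks.
2. Replace the partial regression plot with a check of linearity in the logit, made after the model is fitted, for the continuous predictors: age, D2B time, length of stay and the scale scores. Use a parsimonious method, such as one quadratic or Box-Tidwell term per predictor. Note that such checks may be unstable if one outcome class is small; at 7.05% it would hold only about 12 to 14 patients.
3. Checks for collinearity, separation and influential observations can be named in the same paragraph. Calibration and the c-statistic are optional, since the aim is to identify factors rather than to predict.
4. Keep the normality and variance checks only if the 0–33 score is modelled by linear regression, and say so.

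The cost is one paragraph of wording, with no extra data and no change in sample size.
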